**Appropriate use of anticoagulant therapy**
Frequency of occurrence and proportion of participants with new atrial fibrillation treated with anticoagulant appropriately—via confirmation with general practitioners or participants’ self-reported anticoagulant medication use assessed by using an interviewer-administered questionnaire at 6 months

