### Sample Size

In computing the sample size required to assess the primary feasibility outcome, we will evaluate the proportion of participants reporting being satisfied or very satisfied that their heart rhythm was monitored in the past 6 months in the intervention group versus the control group. We arbitrarily set that 50% of the participants in the control group will be satisfied or very satisfied. With reference to the literature that reported a proportion of 67% [30] to 82% [31] of older people were satisfied or very satisfied with the use of technology-enabled monitoring at home, we postulate that there will be an absolute 30% increase in satisfaction in the intervention group compared with the control group. Our study will have 80% power, using a 5% level of significance, to detect an absolute difference of 30% in satisfaction between the 2 groups. A sample size of 100 participants aged ≥75 years is required to assess the primary feasibility outcome

To calculate the sample size required to evaluate the primary clinical outcome of AF detection rate, we set an AF detection rate of 10% in the intervention group and 1% in the control group, in accordance with a recent study [22]. At 80% power, a 2-sided test, and α .05, we estimate that a sample of 200 participants will be needed to detect a significant difference in AF detection between the intervention and control groups. Therefore, a total of 200 participants will be recruited for this trial to assess the primary clinical outcome.

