### Randomization

Participants will be randomized to the intervention or control group on a 1:1 basis stratified by baseline measure of frailty (ie, frail or not frail according to the FRAIL score) [28,29] and using permuted blocks of sizes 4 and 6. The statistician has generated a randomization list using the RandomiseR package in R software (R Foundation for Statistical Computing) [32]. The randomization list will be input into the REDCap (Research Electronic Data Capture) [33] database, which captures participant demographic and baseline data and survey findings (Multimedia Appendix 1). The statistician and principal investigators will be unaware of patient allocation until after the completion of the study.

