### Analysis

All analyses will be conducted according to the principle of intention-to-treat. Continuous variables will be presented as mean (SD) or median with IQR and categorical variables as frequency and percentage. The key outcomes, namely participant satisfaction in the AF screening program, usability of the screening program, and the incidence of new AF detected over 6 and 12 months, will be reported as frequency and percentages and will be compared between the intervention and control groups using the chi-square test. Comparisons between groups (intervention and control) for other outcomes will be assessed using the chi-square test or Fisher exact test for categorical variables and Student *t* test or Mann-Whitney test for continuous variables as appropriate. We will consider 2-tailed *P*<.05 as statistically significant. The agreement between the ECG device automatic algorithm and clinician interpretation will be evaluated using κ statistics. Subgroup analyses will be performed based on age, gender, and location. Subgroup analysis by frailty will be performed to examine the potential impact of frailty on the outcomes, feasibility, and acceptability of the program. The actual operational costs of delivering the project will be recorded and verified using invoices and receipts, including the costs of personnel involved in interpreting ECGs, which will be computed based on their hourly wages and the time they spent in their roles in this program. The resultant costs will be compared with the costs reported in the literature on the costs associated with the detection of AF in a similar older population. Missing data will be identified, and its causes will be described. Sensitivity analysis will be performed to examine the robustness of the findings [39].

Qualitative evaluation will be reported according to the COREQ (Consolidated Criteria for Reporting Qualitative Research) guidelines [40]. Interviews with patients and GPs will be thematically analyzed using an inductive approach [41]. Themes will be interpreted through the critical realism lens [37] and compared with the literature [42,43]. We will triangulate the quantitative and qualitative findings [44] from patient participants and GPs to acquire an in-depth understanding of the barriers to and enablers of implementing the screening program.

The process evaluation components [36], explanatory data, and anticipated outcomes are summarized in Table 2.

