The quantitative and qualitative analysis approach and methods are summarized in Textbox 1.

**Table 2 table2:** Process evaluation—implementation processes, mechanisms of impact, and contexts.

Process evaluation components	Descriptions	Methods and explanatory data	Anticipated outcomes
Implementation processes	Fidelity of implementation Participation in intervention Reach	Participant enrollment and characteristics, including socioeconomic status and frailty Participant engagement (number of self-recorded ECGs^a^) Clinician characteristics and involvement	Participants who are engaged with the intervention and satisfied with the program
Mechanisms of impact (how does intervention help adoption of AF^b^ self-screening)	Barriers and enablers	Participant engagement and satisfaction Participant survey and interview Clinician survey and interview	A feasible screening program
Context (how do factors external to the intervention affect uptake and implementation)	Participants’ overall health Community-dwelling environment Access to health care services General practitioner views and attitudes	Comorbidities, frailty, and functional status Participant demographic data, survey, and interview Clinician survey and interview	Identification of resources and implementation processes required for effective uptake and implementation of the screening program A contextualized feasible screening program

^a^ECG: electrocardiogram.

^b^AF: atrial fibrillation.

Description of analysis methods on outcome measures compared between the intervention group and waitlist control group.

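### Appropriate anticoagulation is naturally read as a between-arm comparison among detected AF cases only (about 10 versus 1); it should use all randomised participants as the denominator

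*Protocol article*

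**What the plan says.** The Outcome Measurements section of the protocol article lists two clinical outcomes: new AF and appropriate use of anticoagulant therapy. Textbox 1 specifies the second as "Frequency of occurrence and proportion of participants with new atrial fibrillation treated with anticoagulant appropriately". The information comes from the GP or from self-reported "anticoagulant medication use assessed by using an interviewer-administered questionnaire at 6 months".

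The caption of Textbox 1 describes its content as analysis methods for "outcome measures compared between the intervention group and waitlist control group". Separately, the Analysis section assigns other categorical outcomes to a between-group chi-square or Fisher exact test, as appropriate. The same section states: "All analyses will be conducted according to the principle of intention-to-treat".

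The Textbox 1 entry for new AF gives different routes of ascertainment. Monitored participants are identified from ECGs reaching the central monitor. Waitlisted participants are identified by self-report, confirmed by medical records or an ECG.

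**The concern.** New AF is the primary clinical outcome, and the programme exists to find more of it. A denominator of participants with new AF is therefore formed after randomisation, by an event that the intervention affects. The two subsets also differ in kind: mostly screen-detected cases in one arm, and cases found in usual care in the other. A difference between them in the proportion treated could reflect who was found rather than what the programme did. A lack of difference would be equally hard to interpret.

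The conditional proportion also answers a narrower question than the trial's rationale poses. The Introduction argues that early detection matters because it allows anticoagulation. The corresponding effect is how many more people reach appropriate treatment per person offered screening. That effect can be large while the proportion treated among detected cases is equal, or even lower, in the screened arm.

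**Working it through.** **Inputs**
- Detection rates (Sample Size section): "we set an AF detection rate of 10% in the intervention group and 1% in the control group".
- Error rates (Sample Size section): "At 80% power, a 2-sided test, and α .05".
- Total size (Sample Size section): "a total of 200 participants will be recruited for this trial to assess the primary clinical outcome".
- Allocation (Randomization section): "Participants will be randomized to the intervention or control group on a 1:1 basis", hence 100 per arm.
- Dropout: the sample size calculation states no allowance, so 0% is assumed here.
- Share of detected cases treated appropriately: not in the documents. It is assumed below and shown over a range.

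**1. The plan's own figure.** With pooled variance and no continuity correction,

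n per arm = [1.96 × √(2 × 0.055 × 0.945) + 0.8416 × √(0.10 × 0.90 + 0.01 × 0.99)]² / 0.09² = (0.632 + 0.266)² / 0.0081 ≈ 99.5, rounded up to 100.

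The total of 200 is reproduced, and power at 100 per arm is 80.2%. The rates can therefore be used for the next steps.

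**2. Expected denominators at 6 months.** Intervention: 100 × 0.10 = 10. Control: 100 × 0.01 = 1.

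**3. Control cases, Binomial(100, 0.01).**
- P(0) = 0.99^100 = 36.6%. No control proportion then exists.
- P(1) = 100 × 0.01 × 0.99^99 = 37.0%.
- P(at most 1) = 73.6%.
- At the 0.5% control rate that the Introduction reports for the ambulatory patch trial, P(0) = 0.995^100 = 60.6%.

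**4. Most extreme result at the expected counts.** With 10/10 versus 0/1 treated, one of 11 cases is untreated and it is the control. The probability of that table is 1/11, and the only other table with the same margins is more likely. The two-sided Fisher P is 1/11 = .091, so no result at these counts can reach .05.

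**5. Power of the conditional comparison.** This is Fisher's exact test averaged over the binomial case counts, with trials that have no control case counted as non-significant. The treatment shares are assumed.

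| Treated among detected, intervention vs control | Power |
|---|---|
| 80% vs 50% | 2% |
| 90% vs 50% | 4% |
| 90% vs 10% | 14% |
| 100% vs 0% | 26% |

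**6. All randomised as denominator.** The outcome is new AF and appropriately anticoagulated, out of 100 per arm. The treated share is assumed equal in both arms, so the conditional proportions do not differ at all.

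| Share treated | Intervention vs control | Fisher power |
|---|---|---|
| 100% | 10.0% vs 1.0% | 77% |
| 90% | 9.0% vs 0.9% | 70% |
| 80% | 8.0% vs 0.8% | 61% |
| 70% | 7.0% vs 0.7% | 51% |
| 50% | 5.0% vs 0.5% | 27% |

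At 80%, for example, 0.80 × 10% = 8.0% and 0.80 × 1% = 0.8%. The programme would bring about seven more people per 100 to treatment, and the conditional comparison would show nothing.

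**The case against.** The strongest reply is that the text does not commit to the conditional analysis.

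- **The denominator is ambiguous.** The satisfaction entry in Textbox 1 follows the same template, and there the words after participants describe the numerator while the arm is the denominator. Read in parallel, the anticoagulation entry could already mean the proportion of participants who have new AF and are treated appropriately.
- **A count is also named.** Set against about 100 per arm, that count yields the all-randomised proportion.
- **A test is inferred.** The caption of Textbox 1 also covers recruitment, costs and interview themes, which cannot sensibly be compared by arm. The Analysis section names satisfaction, usability and new AF as its key outcomes. Anticoagulation falls under the other outcomes, where the choice of test is left to what is appropriate.
- **The conditional proportion has a use.** Whether detected cases reach treatment is a fair question about care in an implementation trial.

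All of this stands as a limit on the point. A reader might infer that the plan analyses this outcome only among detected cases, cannot follow intention-to-treat, and hides the benefit of screening. The documents do not support that: AF detection and treated counts are both planned, and a count by allocated arm is compatible with intention-to-treat.

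The objection does not remove the defect. No all-randomised denominator is stated for this outcome, the conditional reading is the more natural one, and the Analysis section provides for between-group comparison independently of the loose caption. An analyst who followed the sentence as it stands would probably compute about 10 versus 1.

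**Conclusion.** The point holds for the natural reading of the entry. As a between-arm comparison, the proportion treated among detected AF conditions on a post-randomisation event that the intervention is designed to change. It is also nearly uninformative in this trial: about 10 versus 1 expected cases, a 37% chance of no control case, and P = .091 at best at the expected counts.

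These figures rest on the plan's 10% and 1% rates, 100 per arm with no dropout, and the 6-month time point. They do not describe the period after month 6, when controls are also monitored.

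An all-randomised denominator removes the conditioning and matches the stated intention-to-treat principle. It does not remove the difference in how AF is ascertained in the two arms. Nor does it guarantee adequate power, which ranges from 77% down to 27% as the assumed share treated falls from 100% to 50%. The outcome should therefore be presented as secondary and read mainly through its confidence interval. The primary outcomes and the sample size of 200 are not affected.

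**What to change.** Replace the Textbox 1 entry with wording such as:

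*Number and proportion of all randomised participants, by allocated arm, who have newly detected AF and are appropriately anticoagulated by month 6. Participants without detected AF, or with detected AF but not appropriately anticoagulated, count as no. The arms are compared by Fisher's exact test, with the risk difference and its 95% confidence interval, as a secondary outcome. Among participants with detected AF, the number and proportion treated are described by arm without a test.*

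Fisher's exact test is preferred to chi-square because the event counts will be small. The cost is a few sentences: the same data are collected at the same visit, and the sample size does not change. The change concerns the denominator only and leaves the clinical meaning of appropriate treatment to the investigators.

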**Participant satisfaction at the sixth month**
Frequency of occurrence and proportion of participants reporting being satisfied or very satisfied—assessed via an interviewer-administered questionnaire at 6 months
**Participant recruitment rate**
Number of participants recruited over time—via log sheetCumulative frequency graph over time
**Electrocardiogram transmission to the central monitor**
Frequency of electrocardiogram transmission per participant over the enrollment period—electronic logs of all transmissions to the central monitorThe time the participant transmitted the electrocardiogram—histogram of electrocardiogram transmission time distribution

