**Methods:**

This is a nationwide randomized controlled implementation trial conducted via the internet and remotely among 200 community-dwelling adults aged ≥75 years with no known AF. Randomization will be performed in a 1:1 allocation ratio for the intervention versus control. Intervention group participants will be enrolled in the monitoring program at randomization. They will receive a handheld single-lead ECG device and training on the self-recording of ECGs on weekdays and submit their ECGs via their smartphones. The control group participants will receive usual care from their general practitioners for the initial 6 months and then commence the 6-month monitoring program. The ECGs will be reviewed centrally by trained personnel. Participants and their general practitioners will be notified of AF and other clinically significant ECG abnormalities.

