## Methods

### Study Design

This is a 2-arm, randomized, open-label, waitlist-controlled trial in community-dwelling people aged ≥75 years. We will also conduct a process evaluation of this study. Randomization in the ratio of 1:1 is stratified by participant frailty status (frail or nonfrail; Multimedia Appendix 1). Participant frailty was determined using the FRAIL (Fatigue, Resistance, Ambulation, Illnesses, and Loss of Weight) scale based on five components: *fatigue*, *resistance* (inability to climb stairs), *ambulation* (inability to walk a certain distance), *illness*, and *loss of weight* [28,29]. The intervention group will commence the monitoring program for 12 months upon enrollment. The control group will be waitlisted for the first 6 months and then commence the monitoring program in the subsequent 6 months. The steps involved for enrollment, randomization, intervention, control, and exit from the program are outlined in the study flowchart (Figure 2), and descriptions of the screening program are provided in the following sections.

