### ECG Central Monitoring System

Qualified and trained study personnel, including a cardiac technician and clinical monitoring personnel with medical qualifications, will remotely review all ECGs and compare their diagnosis with the device’s automated diagnostic algorithm. If the ECGs are normal or have minimal abnormalities and the personnel are certain of their diagnosis, the ECGs will not be referred to a cardiologist. However, the personnel will refer all abnormal ECGs for diagnosis confirmation, or uncertain ECG abnormalities for clarification of diagnosis, to cardiologists or cardiac electrophysiology specialists. Participants’ ECGs will be classified into *low, moderate, high, and severe abnormalities* and managed as shown in Table 1. The research team will notify the participants and their GPs of AF or other clinically significant ECG abnormalities. A copy of an abnormal ECG will be forwarded to their GP. When an AF diagnosis is confirmed by the research team, the participant will be advised to see their GP. The participant will exit the screening program or opt to continue the monitoring program. The research team will contact the GP to obtain information about the treatment given to the patient.

**Table 1 table1:** Electrocardiogram (ECG) classification and management plan.

ECG findings	Classification	The study team will take the following actions
First-degree heart block	Low critical abnormality	If PR interval >300 milliseconds, notify and send ECG to GP^a^ within a week If PR interval is between 201 and 300 milliseconds, notify and send ECG to GP within the duration of participant’s enrollment in the study
Ectopic heartbeats (atrial ectopic and ventricular ectopic)	Low critical abnormality	As these are common and noncritical findings, notify GP at the end of the study
Atrial fibrillation, atrial flutter, nonsustained ventricular tachycardia, bradycardia <40 bpm^b^, second-degree heart block, nonsustained supraventricular tachycardia	Moderate critical abnormality	Notify and send ECG to GP within a week Advise patients to see their GP as soon as possible Contact patient to confirm review with their GP in the subsequent week

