### Outcome Measurements

The clinical outcomes include (1) new AF detected over 6 and 12 months and (2) appropriate use of anticoagulant therapy. The feasibility outcomes include (1) participant satisfaction that their heart rhythm was monitored in the past 6 months; (2) participant recruitment rate; (3) frequency of ECG transmission to the central monitor; (4) proportion of participants who complete the program; (5) proportion of dropouts (exit the program prematurely) and reasons; (6) actual costs of the screening program; (6) agreement between the ECG device’s automatic algorithm and clinician interpretation; (7) usability assessment; (8) participant acceptability and barriers to and enablers of implementation; and (9) impact of frailty on feasibility assessments and outcomes.

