**Usability assessment at the 12th month**
Responses to the Usability questionnaire will be assessed by 5-point Likert scale—via self-report questionnaires (Multimedia Appendix 1)

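### ECG transmission, completion, dropout and month-12 usability fall under the between-arm comparisons, although one arm is monitored for 12 months and the other for 6

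*Protocol article*

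**What the plan says.** Under Study Design, "The intervention group will commence the monitoring program for 12 months upon enrollment", whereas "The control group will be waitlisted for the first 6 months and then commence the monitoring program in the subsequent 6 months". The abstract agrees: controls have "usual care from their general practitioners for the initial 6 months and then commence the 6-month monitoring program".

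The textbox that closes the Analysis section is described as covering "outcome measures compared between the intervention group and waitlist control group". Its entries include transmission ("Frequency of electrocardiogram transmission per participant over the enrollment period"), the number and proportion completing the programme, the dropouts, and "Usability assessment at the 12th month". The Analysis section names usability as a key outcome to be compared by chi-square. For the remaining outcomes it provides between-group tests, to be chosen as appropriate.

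Outcome Measurements lists the "proportion of dropouts (exit the program prematurely) and reasons". Under ECG Central Monitoring System, once AF is confirmed, "The participant will exit the screening program or opt to continue the monitoring program".

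By contrast, the textbox fixes new AF, anticoagulant use and satisfaction at 6 months, when the contrast is monitoring against usual care.

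**The concern.** At month 6 the arms differ only in what was randomised. The feasibility outcomes listed above are not tied to that point. Controls cannot transmit while they wait, so they have half the scheduled recording days and half the time on the device in which to leave. When they rate usability, they have half the experience of the device. A comparison of the arms then mixes any difference in engagement with a difference fixed by the schedule.

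A second ambiguity affects dropout. The article lets a participant leave after confirmed AF and describes dropout as leaving early, without saying how the first relates to the second. A successful detection could be logged as a feasibility failure.

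Feasibility is a stated objective, and these outcomes are meant to inform scale-up. A significant arm difference in completion or engagement could be read as evidence about the programme when it is partly an artefact of the timetable.

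**Working it through.** **The plan's own figure.** The article states no figure for these outcomes. Its sample size gives the arm size used below. For AF detection of 10% versus 1%, two-sided α 0.05 and 80% power, with pooled variance and mean proportion 0.055:

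n per arm = [1.960 × √(2 × 0.055 × 0.945) + 0.842 × √(0.10 × 0.90 + 0.01 × 0.99)]² / 0.09² = 99.5, so 100 per arm and 200 in total. This reproduces the article's 200 (power 80.2% at 100 per arm).

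**Transmissions.** Recording is on weekdays (Intervention Group section), about 5 per week.
- Intervention: 52 × 5 = 260 scheduled recordings.
- Control: 26 × 5 = 130.
- The ratio is 2:1 at identical adherence if counts are analysed. A rate per week of enrolment keeps this ratio. A rate per week of monitoring removes it.

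**Dropout and completion.** The article gives no dropout rate, so d, the dropout over 6 months on the device, is an assumption and is shown over a range. With the same constant hazard in both arms, dropout is 1 − (1 − d)² over 12 months and d over 6. The last two columns are exact binomial rejection rates of the uncorrected chi-square test at the 5% level with 100 per arm.

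| Assumed d | Intervention, 12 months | Control, 6 months | Test declares a difference | Same, both arms over 6 months |
|---|---|---|---|---|
| 5% | 9.75% | 5% | 25.1% | 4.4% |
| 10% | 19% | 10% | 44.6% | 5.2% |
| 20% | 36% | 20% | 71.9% | 5.1% |
| 30% | 51% | 30% | 86.6% | 5.1% |

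The table counts only loss while on the device and takes 100 controls as starting it. If losses during the wait were also counted as dropouts, the gap would narrow. At the same hazard throughout, it would close. The article does not say which applies.

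**Usability.** Month 12 means 12 months of use in one arm and 6 in the other. No arithmetic applies: a Likert rating does not accumulate with time, and the direction of any effect is unknown.

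**Exits after AF.** At the planned 10% detection, up to 10 of 100 intervention participants could leave for this reason. With an assumed 10% dropout from other causes, the recorded proportion would be 0.10 + 0.90 × 0.10 = 19% if all of them left, and 0.10 + 0.90 × 0.10 × 0.5 = 14.5% if half did. Monitored controls can leave for the same reason. If their detection once monitored were also 10%, with the same share leaving, this source would add nothing to the arm gap.

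**The case against.** Several points on the other side stand.

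- **Frequency may mean a rate.** A reader might infer that a two-fold difference in transmissions is certain. The documents do not support that, because a rate per monitored week would remove it. Such a rate over 12 months would still include later months that only one arm has, and it would not align completion, dropout or usability.
- **Testing is not certain for every outcome.** The textbox description also covers recruitment, costs and interview themes, which are not naturally arm comparisons. Only usability has a named test. Transmission, completion and dropout are reached through the general sentence on other outcomes, so a test is provided for but not prescribed item by item.
- **AF exits are not stated to be dropouts.** A reader might infer that the plan counts them so. It does not say this. An exit the protocol provides for is not obviously premature, reasons are logged, and the flowchart said to cover exit is not shown. What stands is that the wording permits that reading.
- **The arm that finds most AF need not look worst.** Participants may continue after AF is found, and controls are also screened in months 7 to 12. The planned 1% describes usual care and not controls under monitoring.
- **Usability is taken at the end of the programme in both arms**, which is a comparable stage. The length of use still differs.

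None of this supplies a common window, and the article does fix one for AF, anticoagulant use and satisfaction.

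**Conclusion.** The concern holds for secondary feasibility outcomes. As written, between-arm comparisons of transmission, completion, dropout and month-12 usability are confounded with time on the device.

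The size is conditional. For transmissions it is 2:1 if counts are used. For dropout, the chance of declaring a difference at equal hazards is about 25% to 87% for an assumed 6-month dropout of 5% to 30%, against about 4% to 5% with a common window. This rests on a constant hazard, on 100 per arm starting the device, and on losses during the wait not being counted. For usability neither size nor direction can be given. Misclassification of AF exits is possible, not established.

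It would be wrong to infer that the main results are at risk. The 6-month comparisons of AF detection and satisfaction, and the total of 200, are unaffected. The change is worth making because the feasibility findings are intended to guide wider implementation.

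**What to change.** - Define engagement as recordings divided by scheduled weekdays under monitoring.
- Compare engagement, completion and dropout over each arm's first 6 months on the device: months 1 to 6 for intervention, months 7 to 12 for control. State that calendar time still differs and that controls reach this window only after any waitlist attrition, so the comparison is not purely randomised. Report losses during the wait separately.
- Report intervention months 7 to 12 separately and descriptively.
- Present month-12 usability by arm descriptively, labelled as 12 versus 6 months of use, and not as a test of the intervention.
- Use the logged reasons to report exits after confirmed AF in both arms, apart from dropouts.

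The cost is wording and analysis code. The electronic transmission logs and the log sheets of exits and reasons already hold what is needed. A month-6 usability survey in the intervention arm is not proposed. It would be new data collection, and with enrolment open since May 2021 and 112 enrolled by December 2021, the earliest participants may already have passed that point.
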